### Sample size, power and statistical analysis

#### Sample size and power

A randomised controlled trial will be conducted to evaluate the effectiveness of VIG for parents with premature infants. In comparison with the control group (receiving CAU) it is expected that parents in the intervention group (receiving CAU and VIG) exhibit an enhanced quality in parent-infant interactions and they experience less bonding problems. Bonding problems will be measured with the Postpartum Bonding Questionnaire (PBQ) [67] and the quality of the parent-infant interaction will be measured with the EAS [72].

The sample size calculation is based on the identification of a minimal relevant clinical difference on the EAS subscales of 1.15-1.55 points. Considering a dropout rate of 20-30%, a standard deviation of 1.54 points, power of 80% and a significance level of 5%, an average sample size of 23 (17–29) in each group will be sufficient to detect a clinical relevant difference on the EAS subscales This number has been increased to 35 per group, to allow for the anticipated drop out during the first year.

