### Data analysis

Multilevel modelling will be performed [95]; a flexible regression technique particularly suited for complex longitudinal datasets. To detect clinical significant differences and considering the maximum number of available pre-term infants, the inclusion of 70 infants per group is deemed sufficient. With approximately 100 (high-risk preterm) births a year in the separate specialised hospitals and approximately 150 low-risk premature and 2400 term births in the general hospitals per year, inclusion of 3 x 70 infants and their parents is feasible.

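### The 23 and 35 per group do not carry the stated 80% power at 1.15 points on a two-sided test, dropout is accounted for unclearly, and 35 is not reconciled with 70 per group

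*Protocol article*

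**What the plan says.** The section Sample size and power of the Protocol article compares VIG plus usual care with usual care alone. It takes a "minimal relevant clinical difference on the EAS subscales of 1.15-1.55 points" and "a standard deviation of 1.54 points", with 80% power and a 5% significance level. It does not say whether the test is one- or two-sided.

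Dropout appears twice. The sentence that gives the result opens with "Considering a dropout rate of 20-30" per cent and concludes that "an average sample size of 23 (17–29) in each group will be sufficient to detect a clinical relevant difference on the EAS subscales". The next sentence reads: "This number has been increased to 35 per group, to allow for the anticipated drop out during the first year".

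The following section, Data analysis, uses another group size: "the inclusion of 70 infants per group is deemed sufficient", with three times 70 infants in total. Research design and Randomisation explain the 70s. There are 70 term infants as a non-randomised reference group, plus 70 moderately preterm and 70 extremely preterm infants, who are randomised to control or intervention. No allocation ratio is given.

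**The concern.** Three things do not fit together.

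- **Dropout.** If 17–29 already includes dropout, raising the number to 35 for dropout counts it twice. If it does not, the sentence that introduces 17–29 describes it wrongly.
- **The average.** The stated relevant difference is a range, so its lower end sets the requirement. A number midway between the requirements for the two ends does not secure 80% power at the lower end.
- **The meaning of group.** Adjacent sections give 35 and 70 per group without saying that the word has changed meaning.

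What is at stake is the published justification. As written, a reader cannot tell whether the power statement covers the pooled VIG comparison or a comparison within one gestational-age stratum.

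**Working it through.** **Inputs** (Sample size and power): difference Δ = 1.15 to 1.55 points, SD = 1.54, power 80%, alpha 5%, dropout 20-30%. Assumptions: two-sided test, equal arms, one comparison of means at one time point.

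**Step 1. Reproduce 17–29.** The normal approximation is n per group = 2 × (1.960 + 0.842)² × (SD/Δ)².
- Δ = 1.15: 2 × 7.849 × (1.54/1.15)² = 28.2, so 29. The t-test gives 29.1.
- Δ = 1.55: 2 × 7.849 × (1.54/1.55)² = 15.5, so 16. The t-test gives 16.5, so 17.

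The stated range is reproduced with no dropout in it. The stated average is its midpoint: (17 + 29)/2 = 23.

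**Step 2. The other route to 17–29.** A one-sided 5% test needs 23 per group at 1.15 and 13 at 1.55. Dividing by 1 − 0.20 gives 23/0.8 = 28.75, so 29, and 13/0.8 = 16.25, so 17. The same range therefore also arises from a one-sided test with 20% dropout already included. The document does not say which was used.

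**Step 3. Power at the stated numbers** (two-sided t-test).

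| Evaluable per group | Source | 1.15 | 1.35 | 1.55 |
|---|---|---|---|---|
| 23 | stated average | 70% | 83% | 92% |
| 28 | 35 less 20% | 78% | 90% | 96% |
| 24.5 | 35 less 30% | 73% | 85% | 93% |

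By the normal approximation, the two dropout rows at 1.15 points are 79.8% and 74.3%. The difference detectable with 80% power (t-test) is 1.30 points with 23 per group, 1.17 with 28 and 1.26 with 24.5.

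**Step 4. Enrolment needed for 1.15 points**, as n/(1 − dropout): 29/0.8 = 36.25, so 37; 29/0.7 = 41.4, so 42. Enrolling 35 leaves 29 completers only up to 1 − 29/35 = 17% dropout, which is below the stated range.

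**Step 5. If the test was one-sided.** With 35 enrolled, power at 1.15 points is about 87% after 20% dropout and 82-83% after 30% (t-test and normal approximation). The enrolment needed at 30% is 23/0.7 = 32.9, so 33. There is no shortfall.

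**Step 6. The randomised comparison.** 70 + 70 = 140 preterm infants in two arms is 70 v 70 at 1:1, or 35 v 35 within each gestational-age stratum. After dropout 70 × 0.8 = 56 or 70 × 0.7 = 49 per arm are evaluable. Two-sided t-test power at 1.15 points is 97.5% or 95.5%, and the difference detectable with 80% power is 0.82 or 0.88 points.

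**The case against.** The best defence starts from the wording. The number raised to 35 is most naturally the average of 23, and 23/0.8 = 28.75 (29) and 23/0.7 = 32.9 (33) both lie below 35. So 35 does cover 20-30% dropout for that number. This stands as arithmetic, but it does not help at 1.15 points, because on a two-sided test 23 evaluable per group gives only about 70% power there.

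The second defence is the one-sided route. The hypothesis is directional, the route yields 17–29 with 20% dropout included, and 35 is then enough. This cannot be excluded. It requires a one-sided test that the document never states, and the step to 35 then adds dropout to a figure that already contains it. The text needs correcting on either reading.

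Three stronger readings are tempting, and the documents do not support them:

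- **The trial is underpowered.** It is not, on its own inputs. The comparison of all randomised preterm infants has ample power, and even 35 per group is adequate for 1.35 and 1.55 points at 30% dropout. At 20% dropout the gap at 1.15 points is within rounding of 80%.
- **35 contradicts 70.** The two are compatible if 35 is an arm within one gestational-age stratum. What is missing is the statement that it is. The participant-flow figure was not available for this check, and it may show those cells.
- **35 came from multiplying 29 by 1.2.** The product is 34.8, but the document shows no such step, so this is only a guess at the derivation.

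**Conclusion.** The point holds as a correction of stated figures, not as a must-fix power failure. On the usual two-sided reading, 17–29 is the evaluable number and excludes dropout, contrary to the sentence that introduces it. The average of 23 then falls about 10 percentage points short of 80% power at the smallest difference called relevant. With 35 enrolled the shortfall there is about 2 points at 20% dropout and about 7 at 30%. It is confined to the lower end of the range and disappears if a one-sided test was intended.

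That 35 is unreconciled with 70 does not depend on sidedness. The article's stated hypothesis is a single VIG v control contrast in parents of premature infants, and 35 per group does not describe it. The reassurance about the main comparison assumes 1:1 allocation and a comparison at a single time point. The planned multilevel model of repeated measurements may give somewhat different figures.

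**What to change.** Rewrite the sample-size paragraph; no extra families are needed.

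1. State whether the test is one- or two-sided. If two-sided, say that 17–29 is the evaluable number per group and excludes dropout.
2. Drop the average of 23. The lower end of the relevant difference sets the requirement: 29 evaluable, 37 to 42 enrolled after 20-30% dropout.
3. Base the justification on the randomised comparison: 70 VIG v 70 control, 49 to 56 evaluable per arm after 20-30% dropout, about 95-97% power for 1.15 points and 80% power for 0.82 to 0.88 points. State the allocation ratio, and that the calculation is for one time point.
4. Say what 35 per group refers to. If it is the arm size within one gestational-age stratum, give its power as about 73-78% for 1.15 points, with a detectable difference of 1.17 to 1.26 points.

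The only cost is that any stated within-stratum power becomes slightly less favourable.

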### Data analysis

Multilevel modelling will be performed [95]; a flexible regression technique particularly suited for complex longitudinal datasets. To detect clinical significant differences and considering the maximum number of available pre-term infants, the inclusion of 70 infants per group is deemed sufficient. With approximately 100 (high-risk preterm) births a year in the separate specialised hospitals and approximately 150 low-risk premature and 2400 term births in the general hospitals per year, inclusion of 3 x 70 infants and their parents is feasible.

### Ethical considerations

This study is funded by a Dutch foundation: “Achmea, Foundation Victim and Society”. Ethical and local feasibility approval was obtained for all eight participating hospitals. (Project number: NL24021.060.08, MEC approval: Catharina Hospital, Eindhoven, date: 21-10-2008). All parents will be provided with both verbal and written information about the study and written informed consent is obtained prior to enrolment in the trial.

A data supervising committee will monitor the progress of the study and the inclusion of the parents. No formal stopping rules are in place however funding will only be extended in case of sufficient participating families in the trial.

## Discussion

This is the first prospective study to empirically evaluate the effect of VIG in families with premature infants. The results of this study are relevant for policy, practice and theory for several reasons. Firstly, prematurity constitutes a serious risk factor for adverse parenting. As already mentioned, there are a considerable number of premature births in the Netherlands and a surprisingly high number of infants at risk for child maltreatment. This has become a matter of serious concern for health care policy in general and parents and health care providers in particular. By prospectively examining the process of bonding, this study may contribute to the early detection of bonding problems and adverse parenting. By the use of an easily to administer screening instrument, early bonding problems can be detected and interventions might be suggested. Secondly, the results may also contribute to the implementation of a non-intrusive short-term intervention program for infants at risk for adverse parent-infant interactions (*i.e.*, pre- term infants and infants with pre-peri- and postnatal risk-factors). Family recruitment is expected to be completed in December 2011. First results should be available by 2012.

## Abbreviations

VIG, Video interaction guidance; CAU, Care as usual; GA, Gestational age.
